### Inclusion criteria

Pregnant women 16 years and older who had 28 or more weeks of gestation with a singleton pregnancy and who were seen by a participating gynecologist are eligible to be enrolled in the study. We include women who see only their own gynecologist in both the private office and public health centers during pregnancy.

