### Setting for the trial

The study will be conducted in the primary health care setting of Mashhad, the second largest city in Iran with approximately three million residents. All women who plan to give birth at the two public health care centers and the two private offices can participate in this study if they sign the consent form. The selection of these facilities is based on their readiness for project implementation. Six gynecologists are practicing at the two public health care centers offices, and they see about 1,700 pregnant women per month (250 to 300 returning patients). The two gynecologists in the private offices see about 700 pregnant women per month (100 to 150 returning patients).

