### Study design

This study follows is a randomized controlled trial design. Subjects (pregnant women) are the unit of randomization; they are randomly allocated to each arm of the study. Both the intervention and control group will receive usual care, but the intervention group will also receive the CDA. An independent researcher will centrally perform the randomization by using the computer program on www.randomization.com. Block randomization will be applied to ensure equal group sizes within each center. Because the study is not blinded, we use blocked randomization with randomly selected block sizes of two and four. For each center, the independent researcher will prepare opaque, sequentially numbered, and sealed coded envelopes, with a note for either the decision aid use or not. At each center, the clinic secretary will check eligibility of each pregnant woman visiting the clinic and, if eligible, will provide her with an explanation of the aims and scope of the study and will orally invite her to participate in the study. If the invitee accepts the invitation, then she will be asked to sign the informed consent form. Then the secretary writes the woman’s name and phone number on the next closed envelope. At the end of the day, all envelopes, unopened as of yet, are collected by a research assistant. At the university, this researcher assistant opens the envelopes and allocates the participants of that day to the decision aid or control group. After group allocation, the research assistant will call the participants by phone. Those in the intervention arm will be invited to a software educational session (consisting of 10 women in total) and invited to fill in the paper questionnaires. Those in the control arm will be invited to only fill in the questionnaires. All participants (in the intervention and control arms) will be invited to fill in the questionnaires again two weeks before the expected date of delivery. Blinding of researchers and women is not practical in this study, but the gynecologists are unaware of the patient allocations.

The duration of the intervention is considered from recruitment to the time of delivery. The evaluation of the intervention will be performed at 38 weeks of gestation and before delivery. We will report all cases due to premature delivery.

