### Data collection

Women are asked to complete two questionnaires: the first one upon entering the study and the second one during their 38^th^ week of gestation. Other information (related to women's health status) will be collected from pregnant women’s medical records in the hospitals and clinics.

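### Entry is open from 28 weeks with no upper limit, but the second questionnaire is fixed at about 38 weeks, so late entrants have little or no time with the aid before the outcome is measured

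*Protocol article*

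**What the plan says.** **Entry.** The Inclusion criteria of the protocol article admit "Pregnant women 16 years and older who had 28 or more weeks of gestation with a singleton pregnancy". No upper gestational age is given. The Exclusion criteria cover consent, language, literacy, computer ability, a delivery mode already determined by the physician, and miscarriage or other complications. None of these is a limit on gestational age.

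**Outcome timing.** Three statements fix the second questionnaire, all by gestational age:
- Study design: participants are "invited to fill in the questionnaires again two weeks before the expected date of delivery".
- Study design, later: "The evaluation of the intervention will be performed at 38 weeks of gestation and before delivery".
- Data collection: "Women are asked to complete two questionnaires: the first one upon entering the study and the second one during their" 38th week.

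**Exposure.** Study design says "The duration of the intervention is considered from recruitment to the time of delivery". It sets no minimum time with the aid before measurement. Before use there is a chain of steps: consent at the clinic, collection of envelopes at the end of the day, opening at the university, a telephone call, and then a group session: "Those in the intervention arm will be invited to a software educational session (consisting of 10 women in total"). The software must also be installed on the woman's own computer for use at home (Design of the intervention).

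**Analysis.** The Statistical analysis section applies intention-to-treat to the primary outcomes and handles missing data by multiple imputation.

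**The concern.** The entry rule and the outcome schedule are both stated, and they do not fit together. The time available to use the aid shrinks by one week for each week of gestation at entry, and nothing stops it from reaching zero. A woman can meet every eligibility criterion and still have her second form due within days of consent, or already past due.

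Two different things can then happen. A woman who answers the second form soon after entry contributes a score that reflects little or no use of the aid, which pulls the mean difference towards zero. A woman who enters too late for the second form either fills in both forms at nearly the same time or has no second form, in which case her value is imputed. In all cases it becomes harder to say what exposure the estimated effect refers to. The planned comparison of women's stated decision before and after the intervention (Outcome) has the same difficulty.

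**Working it through.** **1. Time from entry to outcome.** Taking the form as due at 38 weeks, the interval is 38 minus gestational age at entry.

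| Entry (weeks) | Weeks to second form |
|---|---|
| 28 | 10 |
| 36 | 2 |
| 37 | 1 |
| 38 or later | 0 or negative |

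The telephone call, group session and installation all come out of this interval in the intervention arm.

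**2. The time point itself.** On the usual convention of a 40-week expected date (an assumption, as the article does not state it), two weeks before that date is 38 completed weeks. The 38th week, read literally, begins at 37 completed weeks. The statements can therefore differ by up to a week, which matters most for the women with the shortest interval.

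**3. Reproducing the plan's sample size.** Inputs from Sample size: 200 per arm, power 80 %, type I error 5 %, DCS mean 33.6, SD 17.6, target 15 %. Two-sided testing is assumed. Reading 15 % as relative to the mean gives 0.15 × 33.6 = 5.04 points.

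n per arm = 2 × SD² × (1.96 + 0.8416)² / Δ² = 2 × 309.76 × 7.849 / 25.40 = 191.4, so 192 per arm (384 in total).

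This is the closest of the readings tried, but it is not exactly 200. A difference of 15 points would need 22 per arm. A 15-percentage-point drop in a proportion, from control rates of 30 % to 70 %, would need 121 to 174 per arm without continuity correction. The power figures in step 4 therefore rest on the 5.04-point reading, which the article does not state.

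**4. Sensitivity of power.** Suppose a share f of intervention women have no usable exposure, answer the second form, and show no effect. The mean difference is then 5.04 × (1 − f). The standard error at 200 per arm is 17.6 × √(2/200) = 1.76. Power is Φ(Δ/1.76 − 1.96).

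| f | Δ (points) | Power at 200 per arm | n per arm for 80 % |
|---|---|---|---|
| 0 | 5.04 | 81.7 % | 192 |
| 5 % | 4.79 | 77.7 % | 213 |
| 10 % | 4.54 | 73.1 % | 237 |
| 20 % | 4.03 | 63.0 % | 300 |

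The difference detectable with 80 % power at 200 per arm is 1.76 × (1.96 + 0.8416) = 4.93 points. Since 1 − 4.93/5.04 ≈ 0.02, on this reading power drops below 80 % once about 2 % of intervention women are unexposed.

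If the true effect were 15 points, even f = 20 % leaves 12 points, and power remains near 100 %.

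**The case against.** The strongest reply is that a two-form schedule, one at entry and one near 38 weeks, presupposes entry before the second form. On that view this is a gap in wording and not an intention to enrol women after 38 weeks. That is a fair reading of intent, but the eligibility text is what the clinic secretary applies, and it contains no such limit. It also does nothing for women who enter at 36 or 37 weeks.

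A second reply is that a short exposure may be enough. The aid consists of information, a 15-statement preference exercise and self-assessment, used at home. Nothing in the article shows that one or two weeks is too little. This stands: zero effect in late entrants is a boundary assumption in the table above, not a fact about women at 36 or 37 weeks.

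A third reply is that estimating the effect across all third-trimester attenders is a legitimate pragmatic choice, and that late entry falls equally on both randomised arms. The balance argument stands, and the comparison is not biased towards benefit. The pragmatic argument does not cover women whose outcome form is due before they can receive the aid.

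A reader might go further and infer that entry is spread evenly over 28 to 40 weeks. Then 4/12, or 33 %, would enter at 36 weeks or later, and power would fall to about 48 % if none of them showed an effect. The documents do not support this. They give no distribution of entry ages. Each visiting woman is screened, so women under regular care could well be invited soon after 28 weeks, and women with a predetermined delivery mode are excluded.

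A reader might also infer that late entrants both dilute the effect and have their outcomes imputed from exposed women. These cannot both apply to the same woman. She is either observed with little exposure or missing and imputed, and the article does not describe the imputation model.

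**Conclusion.** The point holds as a conflict between two stated rules: entry open from 28 weeks without an upper limit, and an outcome form fixed at about 38 weeks. As written, the plan can randomise women who have almost no time with the aid, and women who cannot complete the two-form schedule at all.

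The harm is lost power and a less clear meaning of the estimate. Its size cannot be taken from the article. On the 5.04-point reading, with SD 17.6, 200 per arm, two-sided 5 % and no effect in unexposed women, there is little slack: power goes from 81.7 % to 77.7 % at 5 % unexposed and to 63.0 % at 20 %. If the intended effect is 15 points, the power loss is negligible. The schedule conflict remains under either reading and should be corrected.

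**What to change.** In the Inclusion criteria, state either an upper gestational age at consent or a minimum interval between receiving the aid and the second questionnaire. The investigators should choose the number, allowing for the telephone call, the wait for a group session, installation and a realistic period of use. If a minimum interval is chosen, define it so that it can be checked at consent and applies alike in both arms. Otherwise it would act as a post-randomisation exclusion in the intervention arm only.

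In Study design and Data collection, use one definition of the second time point, in completed weeks.

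The cost is one line of eligibility text and a wording alignment, with a somewhat smaller eligible pool and possibly slower recruitment. Setting for the trial says of the public-centre gynecologists that "they see about 1,700 pregnant women per month", and gives about 700 for the private offices, so about 2,400 a month against a target of 400. That total counts all pregnant women seen, not those who are eligible, so it suggests room for a limit but does not show how much.

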### Exclusion criteria

Women are excluded if they do not provide a written informed consent, are non-Persian speaking, unable to read and write, or unable to work with a computer. Women whose method of delivery has been predetermined by the physician, based on their clinical condition, are also excluded. In addition, women with miscarriage or other complications are excluded from the study in any group.

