### Statistical analysis

Differences in the primary outcomes will be analyzed using the “intention-to-treat” principle. The mean decisional conflict score and the mean knowledge score will be compared, using the t-test, to the respective means in the control group. Comparing the actual mode of delivery in the intervention and control groups will be based on hospital maternity records and differences will be tested by the Chi square test. We will calculate the Pearson correlation coefficient between the score of decisional conflict and the mode of delivery.

We will handle missing data by a multiple imputation approach. The multiple imputation procedure replaces each missing value with a set of acceptable values that represent the uncertainty about the right value to impute. These multiply imputed data sets are then analyzed by using standard procedures for complete data and then the results from these analyses are combined.

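### The exclusion for miscarriage or undefined other complications most naturally removes randomised women, which conflicts with the stated intention-to-treat analysis

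*Protocol article*

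**What the plan says.** All references are to the protocol article.

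- **Exclusion criteria.** The section first lists items that can be settled at screening: no written consent, language, literacy, computer use, and a delivery mode already fixed by the physician on clinical grounds. It then adds that "women with miscarriage or other complications are excluded from the study in any group". Other complications are not defined by type, severity or date.
- **Study design.** Before consent, "the clinic secretary will check eligibility of each pregnant woman visiting the clinic". The sealed envelopes are collected unopened at the end of the day. At the university a research assistant then "opens the envelopes and allocates the participants of that day to the decision aid or control group". Researchers and women are not blinded; the gynecologists do not know the allocation.
- **Inclusion criteria and Data collection.** Women enter at "28 or more weeks of gestation with a singleton pregnancy", and the second questionnaire falls in week 38.
- **Statistical analysis.** "Differences in the primary outcomes will be analyzed using the “intention-to-treat” principle". Also: "We will handle missing data by a multiple imputation approach".

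**The concern.** An intention-to-treat comparison keeps each randomised woman in the arm to which she was allocated, whatever happens to her later. A rule that takes women out of the study because of something that arises after allocation does the opposite. The two instructions meet in the same data set, and no other section says that women excluded for complications stay in the analysis.

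Two things are at stake. The first is comparability. A complication may change the expected mode of delivery and so, plausibly, decisional conflict. If the proportion removed, or how the removed women differ from the rest, is not the same in both arms, the difference in means shifts. An undefined criterion leaves room for that. The second is precision: the Sample size section states 200 women per arm and mentions no allowance for losses.

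**Working it through.** **1. Timing, from the text.**

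| Step | Section | Do groups exist? |
|---|---|---|
| Secretary checks eligibility | Study design | No |
| Consent signed, name written on closed envelope | Study design | No |
| Envelope opened, woman allocated | Study design | Yes, from here on |
| Up to 38 − 28 = 10 weeks to the second questionnaire | Inclusion criteria, Data collection | Yes |
| Exclusion for complications, in any group | Exclusion criteria | The wording presupposes groups |

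A pure screening rule would not need to mention groups. The post-allocation reading is therefore the natural one, though the article does not state the timing outright.

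**2. Against the analysis section.** Removing randomised women is incompatible with intention-to-treat. The clash with imputation is only partial: imputation can still serve women who remain in the study with missing scores, but a removed woman gets no imputed value.

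**3. Power.** Inputs from Sample size: 200 per arm, 80% power, 5% type I error, mean 33.6, SD 17.6, target 15%. Two-sided testing is assumed.

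The plan's own figure comes first, with the normal approximation n per arm = 2 × (1.960 + 0.842)² × SD² / Δ²:

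- 15% read as relative: Δ = 0.15 × 33.6 = 5.04 points, n = 192 per arm (384 in total).
- 15% read as 15 scale points: Δ = 15, n = 22 per arm.

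Neither gives exactly 200 per arm. The relative reading is the closer of the two, so the power figures are conditional on it. The article gives no complication rate; 5 to 15% is assumed. Two-sample t-test power for 5.04 points, SD 17.6:

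| Removed (assumed) | Left per arm | Power |
|---|---|---|
| 0% | 200 | 81.5% |
| 5% | 190 | 79.5% |
| 10% | 180 | 77.3% |
| 15% | 170 | 74.9% |

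**4. Bias.** Let e₁ and e₀ be the proportions removed in the two arms, and g the number of DCS points by which removed women score above the rest (same g in both arms). Since overall mean = remaining mean + e × g, the remaining mean is low by e × g, and the difference between arms shifts by (e₁ − e₀) × g in size. All values below are assumed.

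| e₁ vs e₀ | g | Shift | Share of 5.04 |
|---|---|---|---|
| equal | any | 0 | 0% |
| 15% vs 10% | 8 | 0.05 × 8 = 0.4 | 8% |
| 15% vs 10% | 15 | 0.05 × 15 = 0.75 | 15% |

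The direction depends on which arm loses more women and on the sign of g. For comparison, the standard error of the difference at 180 per arm is 17.6 × √(2/180) = 1.86 points. Nothing in the article allows a similar calculation for the knowledge score.

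**The case against.** The sentence stands among screening criteria, and eligibility is checked before allocation, so the authors may have meant only complications present at entry. That is possible, and it is why the timing is called inferred. But on that meaning the reference to groups has no function, so the text needs correcting either way. A separate analysis plan would not remove the problem: the conflict is between two statements in this article, not a detail left out.

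A reader might infer that unblinded researchers will delete women knowing their arm. The article does not say so. It does not name who applies the rule, the gynecologists are unaware of allocation, and health status is taken from medical records. Arm-dependent exclusion is possible, not planned. A reader might also suppose that the aid changes how often women consult, and so how often complications are found. Nothing in the article supports that: the aid is software for home use, and both arms receive usual care.

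The objection that the size is modest and rests on assumptions also stands. With equal rates and equal gaps there is no bias. A shift of 0.4 to 0.75 point is 0.2 to 0.4 of the standard error (0.4/1.86 and 0.75/1.86). If the target were truly 15 points, for which 22 women per arm suffice, losing 20 to 30 per arm would hardly matter for power.

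Finally, after fetal loss or delivery before week 38 there is no 38-week decision to measure. That is correct and the fix allows for it. It does not justify removing women with any complication who could still fill in the questionnaire.

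**Conclusion.** The point holds as a conflict in the text. On its natural reading, the exclusion sentence removes randomised women on an undefined criterion, which cannot be combined with an intention-to-treat analysis of the two primary outcomes. It also takes those women outside the planned imputation, although imputation as such can still be carried out for the others. This part needs no arithmetic.

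The consequence is less certain. Bias in the DCS comparison ranges from zero to 0.4–0.75 point under the assumed rates and score gaps. Power falls from 81.5% to 77.3–74.9% if 10 to 15% of women are lost and the 15% target means 5.04 points. The stronger conclusion, that the results will be biased by unblinded deletion, is not supported.

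**What to change.** - Limit the exclusion to complications known before consent, and say so.
- Analyse every randomised woman in her allocated arm. Seek the 38-week questionnaire and the delivery record whatever complications arise later, and impute missing scores as Statistical analysis already plans.
- Where no 38-week decision exists (fetal loss, or delivery before 38 weeks), report the counts by arm.
- Present the complication-free set as a sensitivity analysis only, with other complications defined for that purpose.

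The cost is a change of protocol wording and the collection of a few more questionnaires. The change concerns who is analysed, not clinical care.

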### Data collection

Women are asked to complete two questionnaires: the first one upon entering the study and the second one during their 38^th^ week of gestation. Other information (related to women's health status) will be collected from pregnant women’s medical records in the hospitals and clinics.

### Outcome

The two primary outcomes for the study are the mean of overall decisional conflict and knowledge scores. The decisional conflict will be measured by O’Connor Decisional Conflict Scale (DCS) [25, 30]. The DCS subscales are secondary outcomes, and they will be compared between the two groups of women. The results of this study will show the specific three affected subscales in the pregnant women's decisional conflict scale. Subscale 1 addresses the uncertainty about choosing among alternatives. Subscale 2 addresses factors contributing to uncertainty, including a - feeling uninformed about the alternatives, benefits and risks; b - being unclear about personal value; c - feeling unsupported in making a choice or pressured to choose on course of action. Finally, subscale 3 addresses the perceived effectiveness of the decision [30].

The DCS scale is assessed for validity and reliability using statistical tests, including factor analysis and Cronbach alpha test. A Persian version of the scale was used in 212 pregnant women in Mashhad, Iran.

Knowledge acquisition will be evaluated by 15 true/false questions that are provided by the researchers. The actual mode of delivery, which will be measured by data obtained from hospital records after the intervention. We will determine the studied pregnant women's decision on mode of delivery before and after intervention and compare the results with the actual delivery mode. We will not evaluate cases with emergency delivery but report on them in the two groups.

The acceptability of the CDA by the enrolled pregnant women in the intervention arm will be assessed by interviewing them and analyzing open-ended comments. Our participants' experiences regarding the use of the decision aids will be reported. Also we will discuss our experience with the CDA’s implementation.

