**Methods/Design:**

The protocol concerns a randomized trial study that will be performed among Iranian women. Four hundred pregnant women will be recruited from two private and two public prenatal centers in Mashhad, Iran. They will be randomly assigned to either an intervention or a control group. The designed CDA will be provided to the intervention group, whereas the control group will only receive routine care. The CDA provides educational contents as well as some recommendations. The CDA’s knowledge base is obtained from the results of studies on predictors of cesarean delivery. The CDA’s software will be installed on women’s computers for use at home.

The two primary outcomes for the study are O’Connor’s Decisional Conflict Scale and knowledge as measured by true/false questions. Actual mode of delivery (vaginal versus cesarean) will be compared in the two groups.

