## Background

Caesarian section rate in Iran is three times the global average rate. According to a report released by the Iranian Ministry of Health and Medical Education in 2005, caesarian sections constitute 40.7 % of all deliveries in Iran, including 52 % of the deliveries in Tehran (the capital of Iran), of which 64 % are performed in private hospitals [1]. Over the past 30 years, the rate of caesarian sections has been increased in a referral hospital in Tehran from 14.3 % in 1979 to 22.7 % in 1989, 52.5 % in 1999, and 85.3 % in 2009 [2].

A cross-sectional study on 824 pregnant women in Tehran, reported that 72 % of pregnancies with cesarean section were elective. Of these elective pregnancies, 22 % were performed because of a maternal request. Among pregnant women with these requests, 71 % had no explanation for their request. In addition, 65 % of doctors suggested cesarean delivery for their patients without a true medical indication [3]. Results of a study with 350 questionnaires filled out by pregnant women at waiting time for their prenatal visit in eight public health centers and four private offices in Mashhad, Iran, showed that 90 of these pregnant women (26 %) preferred cesarean delivery when a vaginal delivery was appropriate (unpublished observation). These findings are corroborated by studies showing that 70 % of pregnant women in Iran request cesarean section for reasons unrelated to health needs, such as physician's recommendation, personal request, and compliance to the spouse’s preference [4, 5].

Maternal request is one of the main reasons for increasing the rate of cesarean section in Iran. Cesarean delivery on maternal request (CDMR) is defined as the event in which a pregnant woman prefers and requests a cesarean delivery, without maternal or fetal indication, rather than proceeding with a plan for vaginal delivery [6].

The great variance in CDMR across countries suggests that women need help making a decision about the mode of delivery [6–8]. Gynecologists, midwives, and also the family, have significant effect on pregnant women’s decision on mode of delivery [7, 8]. As a result, the decision-making process may be hindered, for example, a disagreement between a physician and the family (unpublished observation).

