According to Orem's theory [28], decision-making constitutes a first phase of “deliberative self-care.” People who are competent at self-care and understand entirely the courses of actions are usually open to these actions and receptive to their effectiveness. Hence, improving the decision-making process by decision aids has the potential to enhance self-care. Informed decision-making can potentially reduce the over-use of expensive surgical procedures [29].

The objective of our overall project is to design, construct and evaluate a decision aid to help pregnant women choose mode of delivery. The system’s knowledge-base is obtained from the literature on cesarean delivery predictors. Our hypothesis in this study is that decision aid decreases decisional conflict and increases patient knowledge about cesarean and vaginal delivery modes. Decrease in the frequency of cesarean delivery on maternal request is a secondary expected outcome.

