Based on the identified needs in the first step, we developed a computerized decision aid (CDA) system. This computer-based decision support system is an application that pregnant women can use alone or with their families. The program will be installed on a personal computer and/or laptop of pregnant women who are recruited for the intervention group, to be used at home. Capabilities of the installed software include the following:Information retrieval: A list is available of topics that contain information about the types of delivery. Hyperlinks to educational content are also placed in the decision-support section. The included information explains the tradeoffs between vaginal delivery versus CDMR.Clinical data entry: Two categories of information can be entered into the computer by pregnant women. These are listed below.General information (for example, age, gestational age, weight, and height) and health history (for example, parity, history of smoking, drug abuse, and anxiety).Response to 15 statements organized in two categories pertaining to 1) possible reasons for seeking CDMR, such as desire to plan or avoid unplanned cesarean section, and 2) factors that may encourage the selection of natural delivery, such as not requiring anesthesia, surgery or shorter rest after delivery.Decision-support tool: this is an interactive computerized module for supporting the selection of delivery mode. Women are given information about the outcomes associated with vaginal delivery, elective caesarean section, and emergency caesarean section. They can include their personal preferences for possible outcomes by answering questions about 15 statements (section b. clinical data entry). The software program combines the answers and represents the overall results about vaginal delivery versus cesarean section. We also provide an interactive self-assessment and feedback module to educate and correct their misunderstandings about delivery modes.

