### Sample size

We aim to detect absolute decrease of 15 % in the rate of decisional conflict between women in the intervention and control groups. A sample size of 400 pregnant women (200 per trial arm) is needed to detect this difference with a power of 80 % and 5 % risk of type I error. We used O’Connor’s Decisional Conflict Scaling method (0 to 100) to measure decisional conflict (or insecure feeling). The anticipated difference in outcome measure was based on a study assessing decisional conflict based on O’Connor's Decisional Conflict Scale of 212 Iranian pregnant women (mean 33.6; SD = 17.6) [8]. According to the O’Connor’s Scaling Method, decisional-aid tools are most effective when used for subjects with a score of 35 and above [25].

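### The Outcome section sets emergency deliveries aside, while the planned between-arm mode-of-delivery test carries no such exclusion; if the exclusion governs that test, the comparison is no longer between randomised groups

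*Protocol article*

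**What the plan says.** The Outcome section takes actual mode of delivery from hospital records. It then plans to compare women's decisions before and after the intervention with the actual mode, and closes the paragraph with "We will not evaluate cases with emergency delivery but report on them in the two groups". Emergency delivery is not defined and is not limited to cesarean.

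The Abstract (Methods/Design) says "Actual mode of delivery (vaginal versus cesarean) will be compared in the two groups". The Statistical analysis section says "Comparing the actual mode of delivery in the intervention and control groups will be based on hospital maternity records", with a chi-square test. Neither place repeats the exclusion.

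Intention-to-treat is tied to the primary outcomes only: "Differences in the primary outcomes will be analyzed using the “intention-to-treat” principle". The primary outcomes are decisional conflict and knowledge. The Background adds a further target: "Decrease in the frequency of cesarean delivery on maternal request is a secondary expected outcome". The Statistical analysis section gives that target no test of its own.

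**The concern.** Women are randomised at 28 weeks of gestation or later, and emergency delivery comes afterwards. Whether a woman has one can depend on the mode she planned, and shifting that plan is what the aid is expected to do. The protocol itself hints at the link: among possible reasons for seeking CDMR, Design of the intervention lists "desire to plan or avoid unplanned cesarean section".

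Suppose a woman is moved by the aid from a planned cesarean to a planned vaginal birth and then has an emergency cesarean. Under the exclusion she leaves the analysis. Had she kept her original plan, she would have been counted as a cesarean. Selecting on an event that the intervention can influence means the remaining groups are no longer the randomised ones. The result would then estimate neither the actual cesarean rate nor the CDMR rate among all randomised women, yet it could be reported as evidence that the aid lowers cesarean delivery.

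**Working it through.** **Is there a figure to reproduce?** No. The protocol gives no rate, effect or power for mode of delivery; the 200 per arm come from decisional conflict. So the question is which way, and how far, the exclusion moves the result.

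**Inputs**
- Control share planning cesarean: 26%, from the Background ("90 of these pregnant women (26 %) preferred cesarean delivery when a vaginal delivery was appropriate"), used as a proxy. As an alternative, 70%, the share that the same section reports as requesting cesarean for reasons unrelated to health needs.
- A 10-point fall in the intervention arm: assumed.
- Emergency risk e among planned vaginal births, 10/20/30%: assumed.
- Base case, also assumed: every emergency is a cesarean, none arises among planned cesareans, and e is the same in both arms.
- 200 women per arm: Sample size.

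**Formulas.** Let v be the share planning vaginal birth (v0 control, v1 intervention).
- All randomised: cesarean rate = 1 − v(1 − e); arm difference = (v1 − v0)(1 − e).
- Emergencies dropped: cesarean rate = (1 − v)/(1 − ve); arm difference = (v1 − v0)(1 − e)/[(1 − v0e)(1 − v1e)].
- Inflation factor = 1/[(1 − v0e)(1 − v1e)], which exceeds 1 whenever e > 0.

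Example with v0 = 0.74, v1 = 0.84, e = 0.20: all randomised, 40.8% − 32.8% = 8.0 points. Emergencies dropped, 0.26/0.852 − 0.16/0.832 = 30.5% − 19.2% = 11.3 points. Factor 1/(0.852 × 0.832) = 1.41.

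| Planned cesarean, control vs intervention | e | All randomised (points) | Emergencies dropped (points) | Overstatement |
|---|---|---|---|---|
| 26% vs 16% | 10% | 9.0 | 10.6 | 18% |
| 26% vs 16% | 20% | 8.0 | 11.3 | 41% |
| 26% vs 16% | 30% | 7.0 | 12.0 | 72% |
| 70% vs 60% | 10% | 9.0 | 9.7 | 7% |
| 70% vs 60% | 20% | 8.0 | 9.3 | 16% |
| 70% vs 60% | 30% | 7.0 | 8.7 | 25% |

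With 26% vs 16%, the women dropped number 200 × 0.74 × e = 15 to 44 in the control arm and 200 × 0.84 × e = 17 to 50 in the intervention arm.

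**Could it change a conclusion?** Take expected counts at e = 20% with 26% vs 16%. All randomised: 81.6/200 vs 65.6/200, uncorrected chi-square 2.75, p about 0.10. Emergencies dropped: 52/170.4 vs 32/166.4, chi-square 5.73, p about 0.02.

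**Does the direction always hold?** No.
- No effect (v = 0.74 and e = 20% in both arms): 30.5% in each arm after exclusion, so no bias.
- Aid also lowers emergency risk (v 0.74 to 0.84, e 20% to 10%): true difference 40.8% − 24.4% = 16.4 points; after exclusion 30.52% − 17.47% = 13.05 points, an understatement.
- Emergency risk higher in the intervention arm (v 0.74 to 0.84, e 10% to 25%): total cesareans rise from 33.4% to 37.0%, but the reduced set shows a fall from 28.1% to 20.3%.
- Emergencies in 30% of planned cesareans as well (v 0.74 to 0.84, e = 10%): factor 0.95.
- Emergency vaginal births also dropped, 15% of planned vaginal births (v 0.30 to 0.40, e = 5%): factor 0.97.

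**Against CDMR.** If planned cesarean stands for CDMR, its true difference is 10 points and the factor is (1 − e)/[(1 − v0e)(1 − v1e)]. At e = 10/20/30% the reduced set gives 10.6/11.3/12.0 points with 26% vs 16%, but 9.7/9.3/8.7 with 70% vs 60%. The sign of the error depends on which Background figure is used.

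**The case against.** The strongest objection concerns scope. The exclusion sentence directly follows the plan to compare stated decisions with actual mode. There, setting emergencies aside is understandable, because an emergency makes the stated preference uninformative. The places that plan the between-arm test carry no exclusion. So the documents do not support reading the exclusion as a settled rule for the chi-square test. What stands is that its scope is unclear, and the paragraph in which it sits defines the mode-of-delivery outcome as a whole.

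A reader might also infer that the exclusion necessarily exaggerates the aid's benefit. The documents do not support that. They do not say in whom emergencies arise, at what rate, or that they are all cesareans, and the reasons-for-CDMR item is only indirect support. The bias can vanish or reverse.

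It can also be argued that women whose mode was predetermined on clinical grounds are already ineligible, so removing emergencies brings the remaining cesareans closer to CDMR. The aim is reasonable, but a denominator reduced by post-randomisation events is not the way to reach it. Finally, emergencies will be reported by arm, so a reader could rebuild the full comparison if mode is also given. That softens the harm but does not repair the planned test. Both primary analyses are untouched.

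**Conclusion.** The concern holds in conditional form. The Outcome section and the two places that plan the arm comparison must be reconciled. If emergencies are dropped from that comparison, it ceases to be a comparison of randomised groups, whichever way the bias runs.

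The likeliest consequence is that the aid is flattered on total cesareans: by 18 to 72% with planned cesarean at 26% vs 16%, and by about 7 to 25% at 70% vs 60%. Those figures rest on emergencies being cesareans in planned vaginal births, on equal risk in both arms of 10 to 30%, and on an assumed 10-point shift. A claim that the benefit is certainly overstated, or that the effect on CDMR is overstated, would go beyond the documents.

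This should be fixed. It falls short of essential because mode of delivery is not a primary outcome and the trial was not sized on it.

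**What to change.** In the Outcome and Statistical analysis sections:

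1. Make the main mode-of-delivery comparison vaginal versus any cesarean in all randomised women by allocated arm, with emergencies included and counted by their actual mode.
2. Keep the analysis without emergencies only as a labelled sensitivity analysis. State whether the exclusion also applies to the comparison of stated decision with actual mode.
3. Report emergencies by arm and by mode.
4. If CDMR is also compared, use all randomised women as the denominator and count emergency cesareans as not CDMR. Define CDMR as the Background does: a cesarean requested by the woman without maternal or fetal indication, established from her recorded decision together with the hospital record. Absence of a recorded indication is not enough, because it would also capture cesareans suggested by the physician without true indication, which the Background reports as common.

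The cost is protocol wording and, for CDMR, abstracting the indication from hospital records that are already the data source. The cesarean difference may look smaller than with emergencies removed.
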